### Blinding

Both, patients and the entire study staff will remain blinded throughout the complete treatment period of 18 months. Treatment allocations will only be disclosed after the final database lock. Substantial efforts are made to maintain blinding: Since high-dose formulation (oil) does not match the low-dose formulation (tablet), patients in the high-dose arm will take 400 IU tablets in addition to 20.000 IU oil, whereas patients in the low-dose arm will receive an identical volume of placebo-oil in addition to a 400 IU tablet. The patients are primarily handled by a treating physician who is in charge of the evaluation of inclusion or exclusion criteria, adverse events, relapses, side effects, etc. All neurological examinations will be done by an independent evaluating physician. Accordingly, evaluation of all other paraclinical parameters including MRI and OCT will be done by independent examiners. Any patient-related crosstalk between treating and evaluating physicians or examiners is prohibited unless required because of safety concerns. An easy unblinding procedure allows for rapid unblinding of a patient in case of a medical necessity. Unblinding inevitably results in the exclusion of the respective patient.

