**Methods/Design:**

The EVIDIMS trial is a German multi-center, stratified, randomized, controlled and double-blind clinical phase II pilot study. Eighty patients with the diagnosis of definite multiple sclerosis or clinically isolated syndrome who are on a stable immunomodulatory treatment with interferon-β1b will be randomized to additionally receive either high-dose (average daily dose 10.200 IU) or low-dose (average daily dose 200 IU) cholecalciferol for a total period of 18 months. The primary outcome measure is the number of new lesions detected on T2-weighted cranial MRI at 3 tesla. Secondary endpoints include additional magnetic resonance imaging and optical coherence tomography parameters for neuroinflammation and -degeneration, clinical parameters for disease activity, as well as cognition, fatigue, depression, and quality of life. Safety and tolerability of high-dose vitamin D supplementation are further outcome parameters.

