## Methods/Design

### Trial design

EVIDIMS is a national, multi-center, stratified, randomized, controlled, and double-blind clinical phase II trial conducted at approximately ten sites located in or close to Berlin, Germany. Recruitment will start in 12/2011. Eighty patients with relapsing-remitting MS or CIS who are on a stable immunomodulatory treatment with interferon-β1b will be randomized to either high-dose (20.400 IU) or low-dose (400 IU) 25-hydroxyvitamin D supplementation to be taken every other day for 18 months add-on to interferon-β1b. The detailed study design is provided below according to the revised CONSORT statement [27,28]. The study is approved by the local ethics committee and the German Competent Authority (Federal Institute for Drugs and Medical Devices) and is registered at both the European Union Drug Regulating Authorities (Eudra-CT: 2011-002785-20) and Clinicaltrials.gov (NCT01440062). The study will be conducted in accordance to the Declaration of Helsinki in its currently applicable version, the guidelines of the International Conference on Harmonization of Good Clinical Practice (ICH-GCP), and the applicable German laws. All participants will be required to give informed written consent. The trial will be monitored according to ICH-GCP.

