### Randomization and interventions

Eligibility of patients will be determined at the screening visit. At baseline visit, patients who qualified for participation in the study will be stratified according to gender, disease course, and 25-hydroxyvitamin D serum level at screening and then randomized 1:1 into two intervention groups. Group A will receive 20.400 IU cholecalciferol orally every other day; group B will receive 400 IU cholecalciferol orally every other day, which corresponds to the daily dose recommended by the German Nutrition Society http://www.dge.de. In both arms, vitamin D treatment will be add-on to a stable immunomodulatory treatment regimen with interferon-β1b. Regular study visits are carried out after 1, 3, 6, 9, 12, and 18 months. Investigations to be performed on the respective study visits are displayed in table 1. An optional follow-up visit will be offered 24 months after randomization. If necessary, additional unscheduled visits can be performed at any time.

**Table 1 T1:** Time schedule of regular study visits and outcome parameters

	Screening (Week -2)	V0 (Baseline) ± 7 days	V1(Month 1) ± 7 days	V2 (Month 3) ± 7 days	V3 (Month 6) ± 14 days	V4 (Month 9) ± 14 days	V5 (Month 12) ± 14 days	V6 (Month 18) ± 21 days	Follow up (Month 24) ± 8 weeks (optional)
Informed consent	*√*								

In/exclusion criteria	*√*	*√*							

Randomization		*√*							

Evaluation of relapses	*√*	*√*	*√*	*√*	*√*	*√*	*√*	*√*	*√*

Concomitant medication	*√*	*√*	*√*	*√*	*√*	*√*	*√*	*√*	*√*

Physical examination	*√*				*√*		*√*	*√*	

Vital signs	*√*	*√*	*√*	*√*	*√*	*√*	*√*	*√*	*√*

MSFC	*√*				*√*		*√*	*√*	*√*

EDSS	*√*				*√*		*√*	*√*	*√*

ECG	*√*							*√*	

Safety lab	*√*	*√*	*√*	*√*	*√*	*√*	*√*	*√*	

Immunology blood sampling	*√*				*√*		*√*	*√*	

MRI	*√*						*√*	*√*	*√*

OCT	*√*						*√*	*√*	*√*

Visual contrast parameters	*√*						*√*	*√*	*√*

Quantitative motor function tests	*√*						*√*	*√*	*√*

Questionnaires (fatigue, depression, QoL)	*√*				*√*		*√*	*√*	*√*

Cognitive testing (SDMT, FST)	*√*							*√*	*√*

Drug account			*√*	*√*	*√*	*√*	*√*	*√*	

Adverse event reporting			*√*	*√*	*√*	*√*	*√*	*√*	

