### Outcome parameters

The primary endpoint is the cumulative number of new hyperintense lesions on cranial T2-weighted MRI during the treatment period of 18 months. Additional secondary MRI endpoints comprise number and volume of T1-hypointense and T2-hyperintense lesions, proportion of patients without any new T1-hypointense and T2-hyperintense lesions, number of contrast enhancing lesions, brain atrophy as determined by normalized brain volumetry, and changes in brain metabolism as determined by magnetic resonance spectroscopy (MRS). All MRI/MRS investigations will be performed on a 3 tesla MRI scanner (Siemens, Germany). All MRI parameters will be assessed by an experienced evaluator who is blinded to both clinical data and treatment allocation. Secondary clinical endpoints include the annualized relapse rate and the proportion of relapse-free patients. A relapse is defined as de novo development or aggravation or re-occurrence of a preexisting neurological abnormality compatible with MS which lasts a minimum of 24 hours, is separated by at least 30 days from a preceding clinical event and does not occur in the context of fever. Additional secondary endpoints comprise the disease progression as determined by EDSS (evaluated by an independent neurologist), Multiple Sclerosis Functional Composite (MSFC), cognition as determined by the Faces Symbol Test (FST) and the Symbol Digit Modalities Test (SDMT), fatigue and depression as well as quantitative assessment of motor function [31,32]. Additional parameters include retinal nerve fiber layer thickness and macular volume which are increasingly recognized as markers for disease progression in MS [33], visual contrast sensitivity and low contrast visual acuity, 25-hydroxyvitamin D serum levels, and quality of life. Assessment of all endpoints will be done by experienced personnel blinded to both the clinical data and treatment allocation. Peripheral venous blood will be sampled prior and during the intervention for evaluating the effect on cellular and soluble components of the immune system. Safety and tolerability will be assessed by vital signs, safety lab, ECG, and adverse event reporting. The time schedule of all regular evaluations is displayed in table 1.

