### Statistical methods

Evaluation of endpoints will be carried out by both intention-to-treat and per-protocol analyses. Statistical tests and presentation will be appropriate to the category and distribution of the respective variables. Analysis of OCT data will be performed by statistical models which account for intra-patient inter-eye relations. The test level for statistical significance of differences between both treatment arms is defined as p = 0.05 for all tests.

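### The rule that an unblinded patient is excluded is not limited to the per-protocol set, and conflicts with the promised intention-to-treat analysis unless read narrowly

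*Protocol article*

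**What the plan says.** All places are in the protocol article.

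- **Blinding**, on the trigger: "An easy unblinding procedure allows for rapid unblinding of a patient in case of a medical necessity". On the consequence: "Unblinding inevitably results in the exclusion of the respective patient". The second sentence is automatic. It names no analysis set and does not separate study treatment, follow-up and analysis.
- **Statistical methods**: "Evaluation of endpoints will be carried out by both intention-to-treat and per-protocol analyses". No exception is made for unblinded patients.
- **Outcome parameters**, on the primary endpoint: "The primary endpoint is the cumulative number of new hyperintense lesions on cranial T2-weighted MRI during the treatment period of 18 months". On who reads it: "All MRI parameters will be assessed by an experienced evaluator who is blinded to both clinical data and treatment allocation". The Blinding section adds that MRI is evaluated by examiners independent of the treating physician.
- **Table 1**: MRI is scheduled at screening, month 12 and month 18, with a further scan at the optional month 24 visit. Adverse event reporting runs from month 1 to month 18.
- **Trial design**, on the arms: "randomized to either high-dose (20.400 IU) or low-dose (400 IU) 25-hydroxyvitamin D supplementation to be taken every other day for 18 months". The **abstract** adds: "Safety and tolerability of high-dose vitamin D supplementation are further outcome parameters".

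**The concern.** An intention-to-treat analysis keeps every randomised patient in the arm assigned. A rule that removes patients because of something that happened after randomisation works against this unless it is confined to a secondary analysis set, and here it is not confined.

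Unblinding for medical necessity need not be a random event. The doses differ by a factor of 20.400/400 = 51 (IU, with the article's point as thousands separator), and the safety of the high dose is itself under study, so medical events that prompt unblinding could be more frequent in one arm. Serious disease activity could also prompt it, which would tie exclusion to the lesion count. At stake is the comparison that randomisation protects, in a trial with 40 patients per arm. The exclusion also gains nothing for the primary endpoint: revealing the allocation to the treating side does not affect a lesion count made by a reader who is blinded to clinical data and allocation.

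**Working it through.** **1. Readings of the rule, set against the intention-to-treat promise**

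| Exclusion from | Effect on the primary analysis |
|---|---|
| Analysis | Direct contradiction of intention-to-treat |
| The study | Patient can stay in the set by name, but MRI after unblinding is missing |
| The per-protocol set only | None; compatible, but not stated |
| Study treatment only | None if assessments continue; compatible, but not stated |

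Under the second reading the loss depends on timing. A patient unblinded before month 12 would lose both on-treatment scans; one unblinded after month 12 would lose only the month 18 scan.

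**2. The plan's own power figure**

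Inputs from Sample size and Statistical methods: n = 40 per arm, difference 1.5 lesions, power 0.83, alpha 0.05. No SD, test or sidedness is given, so 0.83 cannot be checked independently; it can only be solved for the SD. With a two-sided z-test:

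power = Φ(1.5 / (SD × √(2/n)) − 1.96)

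Setting this to 0.83 at n = 40 gives SD = 2.30. Check: 2.302 × √(2/40) = 0.515; 1.5/0.515 = 2.914; Φ(2.914 − 1.96) = 0.83. A two-sided t-test gives SD 2.27, and a one-sided z-test 2.58. The SD of 2.30 is therefore an assumption.

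**3. Exclusion unrelated to arm and outcome: power only**

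Same formula, SD 2.30, assumed numbers excluded:

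- 2 per arm (n = 38): 1.5/0.528 = 2.840; Φ(0.880) = 0.81
- 4 per arm (n = 36): 1.5/0.543 = 2.764; Φ(0.804) = 0.79
- 6 per arm (n = 34): 0.77

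The one-sided version gives 0.81, 0.79 and 0.77 for the same losses.

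**4. Exclusion from one arm only, of patients with above-average counts, no true effect**

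If k of 40 patients lying g above their arm's mean are dropped:

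- shift in that arm's mean = k × g / (40 − k)
- SE = SD × √(1/40 + 1/(40 − k))
- two-sided error = Φ(shift/SE − 1.96) + Φ(−shift/SE − 1.96)

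With g = 1 SD = 2.30:

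- k = 2: shift 4.604/38 = 0.121; SE 0.521; ratio 0.232; error about 5.6%
- k = 4: shift 9.208/36 = 0.256; SE 0.529; ratio 0.484; error about 7.7%

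With g stated in SD units the SD cancels from the ratio, so these error rates do not depend on the value 2.30. As a sensitivity case, 4 patients at 2 SD above the mean, all in one arm, would give about 16%.

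**The case against.** The Blinding section is operational. It does not mention analysis sets, and exclusion there could mean leaving study treatment or leaving only the per-protocol set. Since the plan provides for both analyses, either meaning agrees with the Statistical methods section. The article also condenses a fuller protocol that may define the term. This stands as far as it goes: a reader might infer that the plan certainly drops unblinded patients from the intention-to-treat analysis, and the text does not establish that. But the sentence carries no qualifier, the two compatible readings are not stated, and later analysis planning cannot recover scans that were never acquired.

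A reader might also infer that patients with safety problems vanish from the safety comparison. Nothing in the article says that recorded safety data are discarded. Adverse events and safety laboratory values are collected at every visit from month 1 to month 18, so an event that prompts unblinding can be recorded. Only follow-up after unblinding is in question, and only if exclusion means leaving the study.

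Finally, a reader might infer a sizeable false benefit for the high dose. With no true effect, that requires exclusion to be linked to both arm and lesion count. Adverse events could differ by arm, but the documents give no reason why those patients would have more lesions. Disease activity relates to lesions, but with no true effect it should arise about equally in both arms. The Background reports good tolerability at high doses without evidence of treatment-related hypercalcaemia, and the eligibility criteria exclude relevant kidney dysfunction, nephrolithiasis and hypercalcaemia, so the number unblinded is probably small. These points limit the size of the problem; they do not reconcile the two sections.

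**Conclusion.** The point holds as a conflict between a stated rule and a stated analysis principle, conditional on what exclusion means. Removal from analysis contradicts intention-to-treat. Removal from the study leaves the 18-month lesion count incomplete for a reason arising after randomisation. Bias is possible but not shown, and its size is unknown because the article gives no unblinding rate.

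The figures are illustrations. A two-sided error of about 5.6% to 7.7% assumes 2 to 4 patients dropped from one arm only, each 1 SD above its mean. Power of about 0.81 to 0.79 assumes 2 to 4 lost in each arm at random and the back-solved SD of 2.30. They do not show that the randomised comparison fails or that the stated power of 0.83 is wrong. The case for changing the sentence is that the rule, followed literally, can only weaken the primary analysis, and that uncollected MRI cannot be recovered later.

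**What to change.** Reconcile the Blinding and Statistical methods sections by replacing the exclusion sentence with one to this effect: a patient who is unblinded remains in the intention-to-treat and safety sets as randomised; continues the scheduled assessments where consent allows, including any remaining month 12 and month 18 MRI read by the blinded evaluator; is flagged as unblinded in the database; and is removed at most from the per-protocol set.

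Whether study treatment continues after unblinding is a separate clinical decision, which this change does not address.

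The cost is a one-sentence protocol change. A few patients continue visits that Table 1 already schedules. Keeping every patient with observed data leaves 40 per arm and hence the stated power of 0.83.

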### Statistical methods

Evaluation of endpoints will be carried out by both intention-to-treat and per-protocol analyses. Statistical tests and presentation will be appropriate to the category and distribution of the respective variables. Analysis of OCT data will be performed by statistical models which account for intra-patient inter-eye relations. The test level for statistical significance of differences between both treatment arms is defined as p = 0.05 for all tests.

## Discussion

In light of the discrepancy between existing epidemiological and preclinical data on the one hand and available clinical data on the other the study design presented here has the potential to substantially contribute to the evaluation of the efficacy of vitamin D supplementation in MS and CIS patients. The randomized, controlled, double-blinded study design and the implementation of independent evaluation of outcome parameters fulfill the criteria for a high-quality clinical phase II trial in MS [34]. Some aspects of the study design however may deserve a closer discussion: Why was an active treatment regimen instead of a placebo treatment chosen for the control arm, i.e. low-dose vitamin D? In fact, this question was heavily debated. Although we do not know whether this represents rather a causal factor or a consequence, serum levels of 25-hydroxyvitamin D are often quite low in MS patients [13,35]. Thus, we expect that low serum levels or even vitamin D deficiency will be detected in a substantial number of screened study candidates. From an ethical point of view and bearing in mind the importance of vitamin D for bone metabolism it would be difficult not to supplement these patients with vitamin D. On the other hand, the daily dose provided in the control arm may not be immunologically active itself as this would prevent the detection of any difference between both groups. Thus, the daily dose recommended by the German Nutrition Society for this group of age which corresponds to 5 μg or 200 IU and which most probably has no immunomodulatory potential represents a compromise between ethical concerns and efficacy aspects. Another important question relates to the dose used in the high-dose arm. In fact, we do not know, at which minimum doses or serum levels vitamin D starts to have immunomodulatory effects. To prevent failure of the trial because of an insufficient treatment dose, we choose the maximum dose for which sufficient safety data are available, which currently corresponds to 10.000 IU per day [23]. It might well be that already smaller doses would be sufficient, but on the other hand it is rather unlikely, that if this dose does not demonstrate any treatment effect, even higher daily doses would do. A further question might be why an add-on regimen to an established immunomodulatory treatment with interferon-β was chosen? In fact, from a methodological point of view, a monotherapeutic design would be preferable. However, since disease-modifying drugs are established and approved for the treatment of MS it would again be unethical to withhold these treatment options in favor of an experimental approach. The restriction to interferon-β as immunomodulatory treatment is explained by the need for maximum homogeneity in the trial cohort on the one hand and the reported synergistic effects of interferon-β and the vitamin D system on the other [18]. Finally, one might suspect that in view of the rather small sample size of 80 participants the study might be underpowered to detect a significant difference between both groups. However, the study will be able to detect a difference in mean new T2-hyperintense lesions per year of 1.5 with a power of more than 0.8. In the pivotal interferon-β1b trial, verum treatment resulted in a reduction of 2.0 lesions per year as compared to a placebo arm [36]. Thus, if high-dose supplementation with vitamin D is indeed effective, a reduction of 1.5 lesions per year would not be unrealistic.

In conclusion, vitamin D has the potential for a safe, orally available and cheap treatment option in MS and the EVIDIMS trial may help to close the existing gap between available promising preclinical and the lacking clinical data on the immunomodulatory efficacy of vitamin D in MS.

### Trial status

The EVIDIMS trial is currently recruiting patients.

## List of abbreviations

CIS: Clinically isolated syndrome; CNS: Central nervous system; ECG: Electrocardiogram; EDSS: Expanded disability status scale; EVIDIMS: Efficacy of Vitamin D Supplementation in Multiple Sclerosis; FST: Faces symbol test; ICH-GCP: International Conference on Harmonization of Good Clinical Practice; IU: International units; MRI: Magnetic resonance imaging; MRS: Magnetic resonance spectroscopy; MS: Multiple sclerosis; MSFC: Multiple sclerosis functional composite; OCT: Optical coherence tomography; QoL: Quality of life; SDMT: Symbol digit modalities test.
